**Methods:**

This study is a single-blinded, randomised controlled trial. Assessments are performed at baseline, after a 12-week intervention, and at a 24-weeks follow-up. Chronic stroke patients (≥ 18 years old, ≥ 6 months post-stroke) able to stand for 3 min, independently walk 10 m, follow a two-stage command, and without other neurological diseases apart from cognitive deficits or dementia are included. Participants in the intervention group perform the exergame training twice per week for 30 (beginning) up to 40 (end) minutes additionally to their usual care programme. Participants in the control group receive usual care without additional intervention(s). Global cognitive functioning (total Montreal Cognitive Assessment (MoCA) score) is the primary outcome. Secondary outcomes include health-related quality of life, specific cognitive functions, single- and dual-task mobility, and spatiotemporal gait parameters. The target sample size for this trial is 38 participants. Linear mixed models with the post-outcome scores as dependent variables and group and time as fixed effects will be performed for analysis.

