### Objectives {7}

To address the gaps of knowledge regarding rehabilitation of cognitive functions and effects of motor-cognitive exergames in chronic stroke, the primary objective of this study is to evaluate the effect of a 12-week concept-guided, personalised, motor-cognitive exergame training when added to usual care, in comparison to the effect of usual care alone on global cognitive functioning in chronic stroke survivors.

The secondary objectives of this study are to explore (1) the acute and (2) the persistent effect up to a 12-week follow-up of the exergame intervention on health-related quality of life, specific cognitive functions (sub-functions of attentional, executive, and visuospatial functions), single- and dual-task mobility, and spatiotemporal parameters in chronic stroke patients.

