## Outcomes {12}

Primary and secondary outcomes are collected at three time points (T0–week 0, T1–week 12, T2–week 24; see Table 2, Figs. 1 and 3) by cognitive and motor assessments as well as a health-related-quality-of-life questionnaire. At the baseline measurement (T0), participant characteristics and baseline factors are recorded. Intervention and activity outcomes are collected during the intervention (T0–T1) and the follow-up (T1–T2) periods, respectively. All variables will be aggregated as means or medians, depending on the distribution of the data, and the analysis metric for all will be final values (see the ‘ Statistical methods’ section). An overview of all outcome variables is presented in Tables 3 and 4.

**Table 2 Tab2:** Overview over outcome recording. *ADH*, adherence; *BBS*, Berg Balance Scale; *BQ*, baseline questionnaire, incl. see the ‘ Baseline factors’ section; *TUG(-Cogn)*, (cognitive dual-task) Timed Up and Go test; *CPL*, compliance; *FAC*, Functional Ambulation Category; *FM-LE*, lower-extremity component of Fugl-Meyer assessment; *MoCA*, Montreal Cognitive Assessment; *mRS*, modified Rankin scale; *MRT*, mental rotation test; *NBT*, N-back test; *NIHSS*, National Institute of Health Stroke Scale; *OWA*, outdoor walking assessment; *PCA*, physical and cognitive activities; *PP*, perceived performance; *PTD*, perceived task difficulty; *SIS 3.0*, Stroke Impact Scale; *SRT*, simple reaction test; *Stroop*, Stroop Interference test; *TMT*, Trail Making test; *UC*, usual care; *10MWT*, 10-m walk test

Time (weeks)	0	+ 1–12	+ 12	+ 13–24	+ 24
**Time point**	Baseline (T0)	Intervention period	Post-intervention (T1)	Follow-up period	Follow-up (T2)
**Study staff**	Assessor	Training supervisor	Blinded assessor	Training supervisor	Blinded assessor
**Baseline factors:** BQ, NIHSS, FAC, mRS, BBS, FM-LE	+				
**1° Endpoint:** MoCA	+		+		+
**2° Endpoints:** SIS 3.0, SRT, TMT, Stroop, NBT, MRT, TUG(-Cogn), 10MWT, OWA	+		+		+
**Intervention Endpoints:** CPL, ADH, PTD, PP		+ *(intervention group only)*			
**Activity Endpoints:** UC, PCA		+		+

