### Primary outcome

The primary outcome is global cognitive functioning measured by the total score of the Montreal Cognitive Assessment (MoCA) [93]. The MoCA is composed of several tests assessing different cognitive domains including attention, executive functions, working memory, short-term memory recall, visuospatial skills, and orientation [74]. The MoCA has been successful in detecting cognitive decline [94] and showed good reliability in stroke patients and healthy older adults [95–97] as well as fair to good responsiveness and validity [98] in chronic stroke patients [99]. The maximum achievable score is 30 points, where more points represent better cognitive functioning. For individuals with 12 or less years of education and a total score < 30, an additional point is added [93]. A MoCA score below 24 points indicates mild cognitive impairment in individuals after stroke [74, 100, 101], and an improvement of 1.22 points was found to be a clinically relevant change [99].

Global cognitive functioning, measured by the total score of the MoCA, covers the cognitive domains typically impaired after stroke. Further cognitive tests examining specific cognitive domains/functions will be implemented as secondary outcomes [102].

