Assumptions on the residuals of primary and secondary outcomes will be checked using the DHARMa package in R [147]. Appropriate actions will be taken if one or more assumptions are not met. All primary and secondary outcomes will be analysed following the standard intention-to-treat (ITT [148, 149]) principle using linear mixed-effects models (LMEM, lme4 package in R). Subject-specific random intercepts will account for within-subject correlations between time points. Follow-up scores (T2) of the outcomes will be the dependent variables of the models, while group (intervention vs. control, control being the reference), time (T0, T1, T2), and group x time interactions at T1 and at T2, respectively, will be included as independent variables (fixed effects). Baseline factors such as age, sex, and time since stroke will be considered as covariates. Missing data of whole measurement time points (i.e. of dropouts) will be accounted for with the ‘last observation carried forward’ method. For single missing data points (e.g. if a participant did not perform an assessment at one time point or a technical issue produced missing data at one time point), however, no data imputation will be performed as LMEMs can be fitted even if some outcome data are missing [145, 150]. For the outdoor walking assessment (OWA), high occurrence of missing data is expected, as ability to walk 400 m is not covered by the eligibility criteria and varying weather conditions on the measurement days may interfere with the assessment. Therefore, for the OWA outcome parameters, datasets of participants who did not perform the OWA at one or several time points will be excluded from the analysis. Significance will be set to *p* < 0.05. Effect sizes will be calculated as *r* (Bravais-Person correlation coefficient) and interpreted as small (*r* < 0.3), medium (*r* < 0.5), and large (*r* ≥ 0.5) [145].

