### Methods for additional analysis (e.g. sub-group analyses) {20b}

As the ITT analyses may underestimate a present treatment effect [148], the analyses of the primary and secondary outcomes will be repeated with only those participants, who did not withdraw from the study within the intervention period (T0–T1), and with adherence rates of ≥ 85% (per protocol analysis). This cut-off was chosen based on systematic reviews covering comparable interventions, outcomes, and populations [27, 151], where a minimum of 720 min in at least 12 weeks or an intervention duration of at least 8 weeks were recommended. Moreover, 85% of 24 training sessions results in an ‘acceptable’ absence of 3.6 sessions, which seems practical to account for sickness and conflicting schedules. The results of the ITT and per-protocol analyses will be compared in the discussion of the study report.

Furthermore, to assess clinical meaningfulness of possible treatment effects, the following analyses will be performed on outcomes that (a) revealed a significant between group effect at either T1 or T2 [152, 153] and (b) a clinically important difference is reported in literature. On the one hand, the difference in change score between the two groups will be compared to clinical meaningful change scores (e.g. 1.22 points in the MoCA [99]). On the other hand, frequencies of ‘responders’ (individual change score above clinically meaningful change) and ‘non-responders’ (individual change score below clinically meaningful change) between the two groups will be compared [152, 153].

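### The primary model takes the week-24 score alone as its response, so its time and interaction terms cannot be estimated; the model probably intended gives two unranked primary contrasts.

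*Protocol article*

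**What the plan says.** The model is set out in Statistical methods for primary and secondary outcomes {20a}:

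- **Response:** "Follow-up scores (T2) of the outcomes will be the dependent variables of the models".
- **Fixed effects:** group, plus "time (T0, T1, T2), and group x time interactions at T1 and at T2, respectively, will be included as independent variables (fixed effects").
- **Random effects:** "Subject-specific random intercepts will account for within-subject correlations between time points".
- **Significance:** p < 0.05, with no division between visits.

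The abstract describes the response differently: "Linear mixed models with the post-outcome scores as dependent variables and group and time as fixed effects will be performed for analysis".

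Other sections that could settle the visit do not:

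- **Outcomes {12}:** "Primary and secondary outcomes are collected at three time points (T0–week 0, T1–week 12, T2–week 24").
- **Primary outcome:** "The primary outcome is global cognitive functioning measured by the total score of the Montreal Cognitive Assessment (MoCA"), with no visit attached.
- **Objectives {7}:** "the primary objective of this study is to evaluate the effect of a 12-week concept-guided, personalised, motor-cognitive exergame training". Here 12 weeks is the length of the training. The split into acute and persistent effects is written only for the secondary objectives.
- **Sample size {14}:** a two-way mixed ANOVA with three measurements, without naming the effect being tested.

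**The concern.** There are two linked problems.

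First, the stated response does not fit the stated model. A time factor with three levels, interactions at two visits and a random intercept for correlation between visits all need repeated responses per participant. The T2 score supplies one. The abstract's post-outcome scores do not name the same response, so an analyst working from {20a}, from the abstract or from the three-measurement sample size would set up different models.

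Second, repairing the response does not settle the primary test. The repaired model gives a week-12 contrast, a week-24 contrast and a joint interaction test. A superiority trial with one primary outcome then has three candidate primary tests and no order among them. If the choice is made after the results are seen, the primary claim can follow whichever visit is significant.

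**Working it through.** **1. Can the model be estimated as printed?**

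The fixed effects are an intercept, group, two time terms and two interaction terms, six columns in all. I took 38 participants, the planned number.

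- *T2 rows only.* There is one row per participant. Time is constant, so each time and interaction column is either zero or a copy of the intercept or group column. The 38 × 6 design has rank 2. Only a mean and a group difference at week 24 can be estimated. With one row per participant, the random-intercept variance cannot be separated from the residual variance.
- *T2 score repeated over three rows per participant* (simulated data). The response does not vary within a participant. The time and interaction coefficients are exactly 0, the residual variance collapses to about 0 and the random-intercept variance diverges.
- *Score at each visit as response* (simulated data). The same model fits normally and returns separate group × T1 and group × T2 coefficients.

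**2. What does N = 38 correspond to?**

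Inputs from Sample size {14}: f = 0.21, alpha 0.05, power 0.80, 2 groups, 3 measurements, correlation 0.5, nonsphericity correction 1.

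For the group × time interaction under the G*Power convention:

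- λ = f² · N · m / (1 − ρ) = 0.0441 × 38 × 3 / 0.5 = 10.05
- df1 = (2 − 1)(3 − 1) = 2; df2 = (38 − 2)(3 − 1) = 72
- Power = 0.8003 at N = 38 and 0.776 at N = 36

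The stated N is reproduced. The between-group variant would need 122. The within-factor main effect also gives 38, but it does not compare the groups, so the joint 2-df interaction is the group comparison that matches the stated size.

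**3. Error rate if either visit could carry the claim**

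Under equal correlation between visits, the changes T1 − T0 and T2 − T0 share the baseline:

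- Var(T1 − T0) = Var(T2 − T0) = 2(1 − ρ)σ²
- Cov = (1 − ρ)σ², so the correlation is 0.5

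P(|Z1| > 1.96 or |Z2| > 1.96) for a bivariate normal with no true effect:

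| Correlation | Either visit at 0.05 |
|---|---|
| 0.5 | 9.1% |
| 0.7 | 8.3% |
| 0.8 | 7.8% |
| 0 (independent) | 9.75% |

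A single named contrast, or the joint test alone, stays at 5%.

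**4. Power if one contrast is named**

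Suppose the groups are equal at T0 and differ by d (in SD units) at both T1 and T2. The interaction effects are then ±d/3, ±d/6 and ±d/6.

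- Sum of squares over the six cells = 2(d²/9 + d²/36 + d²/36) = d²/3
- f² = (d²/3)/6 = d²/18, so d = 0.21 × √18 = 0.89
- A gap at one visit only gives the same d for that visit.

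With ρ = 0.5 the change-score variance is 2(1 − 0.5) = 1 in SD² units. With 19 per group the standard error is √(2/19) = 0.324.

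| True gap (SD) | Noncentrality | Power, 36 df | Power, 72 df |
|---|---|---|---|
| 0.89 (implied by f = 0.21) | 2.75 | 76.2% | 77.3% |
| 0.44 (cited SMD for global cognition) | 1.36 | 26.2% | 26.8% |

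The 72 df are those of the pooled within-subject residual in the repeated-measures model.

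**The case against.** The strongest reply is that the defect in the response comes down to one parenthesis. The three time levels, the random intercept between time points, the interactions at both visits and the three-measurement sample size all point to the score at each visit as the response, and a statistician would fit that model. This is fair as a reading of intent, and I accept it. It does not make the printed sentence right. The article defines T2 as week 24, so the sentence names one specific visit. The reply also leaves the second problem in place.

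A second reply is that the primary visit may be named in an analysis plan that is not shown. Silence alone would not be a finding. Here, however, the article does state its primary model, and it points the response at a visit that cannot support the terms listed.

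Three stronger readings are tempting and are not supported:

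- *That the plan counts a success at either visit.* Methods for additional analysis {20b} does refer to outcomes that "revealed a significant between group effect at either T1 or T2". That phrase only selects outcomes for the clinical-meaningfulness and responder analyses. It is not a decision rule for the primary outcome, so 9.1% is not the trial's declared error rate. If the joint test were primary, the error would be 5%. If the visit contrasts were read only after a significant joint test, a false visit claim under no effect would occur about 4% of the time.
- *That week 24 becomes the headline result.* A model whose terms cannot be estimated has no headline, and the same sentence also lists an interaction at T1.
- *That the documents make week 12 primary.* It is the natural reading of an objective about a 12-week training, but no section says so.

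The abstract's omission of the interaction is ordinary condensation. Only its different description of the response matters.

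**Conclusion.** The point holds as a contradiction in a stated analysis rule. With T2 alone as response, the time and interaction terms and the random intercept are not estimable, and the abstract names a different response. The model probably intended can be fitted, but it leaves a week-12 contrast, a week-24 contrast and a joint test with no ranking and no alpha split.

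The size of the second part is conditional. The false-positive rate is about 9.1% only if either visit at 0.05 may carry the primary claim and the two contrasts correlate at 0.5, which follows from the plan's own correlation under compound symmetry. It is 8.3% at correlation 0.7. Any single named test removes the excess. The power figures assume 19 per group, correlation 0.5 and, for the 0.89 SD gap, equal effects at T1 and T2 (or an effect at the tested visit only).

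**What to change.** In {20a}, state that the response is the MoCA score at each visit (T0, T1, T2), and use the same description in the abstract. Before analysis, name one primary test at two-sided 0.05. The choice is the sponsor's:

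- The group × T1 contrast fits the objective of a 12-week training best.
- The joint 2-df interaction is the group comparison that reproduces N = 38.

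Make the remaining contrasts secondary, either tested in a fixed order after the primary test or reported with 95% confidence intervals. The either-visit wording in {20b} can stay, because it only opens the clinical-meaningfulness and responder analyses.

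No new data, participants or procedures are needed. The sponsor gives up a second chance at a primary claim. If a single contrast is chosen, the change goes beyond wording, because the power statement must be redone: about 77% instead of 80% at N = 38 for the 0.89 SD gap implied by f = 0.21, and about 27% if the true gap is the cited SMD of 0.44. Keeping the joint test as primary preserves the stated 80%, but a significant result would not by itself say at which visit the groups differ.

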### Trial design {8}

This study is a randomised, controlled trial (RCT) with two parallel arms, investigating the superiority of a concept-guided, personalised, motor-cognitive exergame training added to usual care over usual care alone. The trial employs a single-blinded approach, with outcome assessors being unaware of group assignments. The randomisation is performed with a 1:1 ratio using stratification by sex (female or male [73]) and cognitive impairment (MoCA ≥ 24 or MoCA < 24 [74]).

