## Assignment of interventions: allocation

### Sequence generation {16a}, concealment mechanism {16b}, and implementation {16c}

The randomisation is stratified by cognitive status (cognitive impairment absent or present, determined by a MoCA score ≥ 24 or < 24, respectively [74, 100, 101]) and by sex (female or male [138–140]). Both stratifying variables are allocated 1:1 to both groups. Participants are randomised using REDCap, the same tool as utilised for eCRF keeping (see the ‘Data management’ section [141, 142]). To perform the randomisation in REDCap, a pre-defined randomisation list in the form of an excel document needs to be uploaded onto the platform, which is then being used by the software. Instructions by REDCap show how this list must be structured to provide the desired allocation ratio and stratification [141, 142]. These instructions were followed by the randomisation-list creator, a person otherwise not involved in the study. This way it was ensured that no member of the study team would know the allocation sequence. After creating the list, the randomisation-list creator encrypted the excel document containing the list with a password. Both, the list and the password, are stored in a secure place, where the investigators of the study team have no access. Moreover, the REDCap user rights to access and view the randomisation setup feature were removed from all investigators of the study team before the final randomisation list was uploaded onto the REDCap platform [141, 142].

Study investigators other than the blinded assessor enrol participants and allocate them to groups. A separate instrument in REDCap, which is invisible for the assessor through user privileges, is used for randomisation.

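### The primary mixed model does not use baseline MoCA efficiently: as written it tests a difference in change, or on its other reading ignores baseline altogether

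*Protocol article*

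**What the plan says.** Statistical methods {20a} describes one linear mixed model for all primary and secondary outcomes:

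- Covariance: "Subject-specific random intercepts will account for within-subject correlations between time points".
- Fixed effects: group (control as reference), time with levels T0, T1 and T2, and "group x time interactions at T1 and at T2, respectively, will be included as independent variables (fixed effects".
- Dependent variable, in the same sentence: "Follow-up scores (T2) of the outcomes will be the dependent variables of the models".
- Covariates: "Baseline factors such as age, sex, and time since stroke will be considered as covariates". Baseline MoCA is not named here, nor in the list under Baseline factors.

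The Methods paragraph of the abstract gives post-intervention scores as the dependent variables, and Outcomes {12} states that "the analysis metric for all will be final values".

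On allocation, Trial design {8} says: "The randomisation is performed with a 1:1 ratio using stratification by sex (female or male [73]) and cognitive impairment". The section on sequence generation {16a} repeats this: "The randomisation is stratified by cognitive status (cognitive impairment absent or present, determined by a MoCA score ≥ 24 or < 24, respectively".

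**The concern.** A model with T0, T1 and T2 as time levels needs the T0 score in the response. A response made only of T2 scores, or only of post scores, cannot carry that time factor. The text therefore supports two models:

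- **T0 in the response.** The group term is a free baseline difference and the T1 interaction compares mean changes. Because groups are randomised, the expected baseline difference is zero, and estimating it costs information.
- **Post scores only.** There is no change-score contrast, but baseline MoCA then plays no part in the analysis, since no section commits to it as a covariate.

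Baseline MoCA is collected on everyone and drives the stratification. In a trial of 38, precision on the primary outcome that is available without new data should not be left unused.

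**Working it through.** **Inputs.** From Sample size {14}: N = 38 (19 per group), f = 0.21, α = 0.05, power 0.80, 2 groups, 3 measurements, correlation ρ = 0.5, and SMD 0.44 as the cited review estimate for global cognition. Assumed: ρ of 0.7 and 0.8 as alternatives, the percentile at which MoCA 24 cuts the sample, and the block size.

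**1. The plan's own figure.** For the group x time interaction, λ = f²·N·m/(1−ρ) = 0.0441 × 38 × 3 / 0.5 = 10.05, with 2 and 72 degrees of freedom. Power is 0.8003 at N = 38 and 0.776 at N = 36, so 38 reproduces. The between-group variant would need 122. The trial was therefore sized on the same free-baseline interaction that the first reading tests.

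**2. What the T1 coefficient is.** In a simulated balanced data set, the group x T1 coefficient of the planned model was −0.01197, equal to the difference in mean change to numerical precision. This holds when time points are complete or filled by last observation carried forward. Adding sex and age as main effects left the coefficient and its standard error (0.305) unchanged. Dropping the group main effect, so that baseline means are equal, lowered the standard error to 0.252 in that data set.

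**3. Variance under simple randomisation** (units of σ², multiplied by 2/n for the contrast).
- Change: 2(1−ρ) = 1.00 at ρ = 0.5, the same as ignoring baseline.
- Baseline-adjusted or constrained: 1−ρ² = 0.75.
- Ratio: (1+ρ)/2 = 0.75 at ρ = 0.5, 0.85 at 0.7 and 0.90 at 0.8.
- With 19 per arm, the standard errors at ρ = 0.5 are √(1.00 × 2/19) = 0.324 and √(0.75 × 2/19) = 0.281. Power for SMD 0.44 is 0.26 and 0.33.

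**4. Allowing for stratification on baseline MoCA.** Simulation of 20,000 trials, stratified at an assumed median cut:

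| ρ | True SD, change | True SD, adjusted | Variance ratio | Mean model SE, change | SE / true SD, change | Type I error, change | Type I error, adjusted |
|---|---|---|---|---|---|---|---|
| 0.5 | 0.300 | 0.285 | 0.90 | 0.323 | 1.08 | 0.035 | 0.051 |
| 0.7 | 0.240 | 0.234 | 0.95 | 0.250 | 1.04 | 0.038 | 0.050 |
| 0.8 | 0.200 | 0.197 | 0.97 | 0.204 | 1.02 | 0.045 | 0.052 |

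A second simulation used blocks of 4 within sex by MoCA strata, with the cut at the 50th or 30th percentile. It gave true variance reductions of 11–14% at ρ = 0.5, 5–6% at 0.7 and 3–4% at 0.8. Across the checks, the standard error at ρ = 0.5 was overstated by 6–8%.

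**5. Power under stratification.** The planned test pays twice: a modestly larger true variance and an overstated standard error. Power for SMD 0.44 at ρ = 0.5 therefore still moves from about 0.25 to about 0.33, close to step 3.

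**The case against.** The strongest reply is that a random-intercept model with group, time and their interaction is conventional and valid, matches the sample-size calculation, and does not inflate false positives. All of that stands. The plan does not rely on precision that it fails to deliver.

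Three stronger readings are tempting and are not supported.

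- **A 25% variance loss, so that adjustment makes 38 behave like about 51 (38/0.75).** This assumes simple randomisation. Stratifying at MoCA 24 already removes much of the chance imbalance. In true precision the equivalent is about 42 to 44 (38/0.90 to 38/0.86). The rest of the loss is conservatism in the standard error.
- **Bias through regression to the mean.** Given a chance baseline difference D, the change estimate shifts by −(1−ρ)D. That shift averages to zero over randomisations, and stratification limits D for the primary outcome.
- **Leaving sex as a factor to be considered costs precision in the planned model.** A sex main effect cannot alter the group x time contrast (step 2). An article may also leave the final covariate list to the full protocol or analysis plan. Sex matters only once the model is baseline-adjusted or constrained.

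It can also be said that the post-score reading removes the change-score argument. It does, but it leaves baseline MoCA unused, so the remedy is the same.

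**Conclusion.** The point holds as a matter of efficiency and clarity. The article contradicts itself on the dependent variable, and neither reading makes good use of baseline MoCA. At ρ = 0.5, adjustment would cut the true variance of the T1 contrast by about 10–14%, correct a standard error that is 6–8% too large (type I error about 0.035 as planned), and raise power for SMD 0.44 from about 0.25 to 0.33. At an assumed ρ of 0.7 the true variance gain is about 5–6%, and at 0.8 about 3–5%.

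The variance, standard-error and type I figures describe the reading with T0 in the response. They rest on the assumed stratum cut and block size and on complete or carried-forward time points. A reader might infer that the planned estimate is biased or that the trial is wrongly sized for its model; neither follows. This change should be made because it is nearly free, not because the planned test is invalid.

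**What to change.** 1. State one dependent variable, and make Statistical methods {20a}, Outcomes {12} and the abstract agree.
2. Specify the primary model with MoCA at T1 and T2 as the response, and with continuous baseline MoCA, visit, group, group x visit and sex as fixed effects, keeping the subject random intercept. Continuous baseline MoCA also covers the cognitive stratum. Sex enters as the other stratification factor.
3. Alternatively, keep T0 in the response, constrain the baseline means to be equal by dropping the group main effect, and add sex.
4. Use the same form for each secondary outcome with its own baseline.

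The cost is wording in the statistical section and about one or two degrees of freedom. No new data are needed, and N = 38 need not change. The choice should be recorded before the outcome data are analysed by group.
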